## 2.3 Randomization

Randomization is part of the parent study. All details are included in that protocol.

## 2.4 Blinding

The blinding codes are not maintained or accessible by SCHARP staff or any members of the IDCRC SDSU and will only be provided to SCHARP after the lock of the database for this study.

## 2.5 Sample Size and Power

Very little data are available on incidence rates of SARS-CoV-2 infection in children aged 12-17. The CDC (<https://www.cdc.gov/coronavirus/2019-ncov/cases-updates/burden.html>) estimates a cumulative incidence in children 5-17 years old of 27,218 per 100,000 from February 2020-December 2021 which translates into approximately 5.7 per 1,000 person-weeks. A similar incidence estimate can be calculated based on prevalence in children presenting for non-COVID-19 related hospital visits in the summer of 2020 (Sola et al, JAMA Pediatr 2021). When estimating power for the protocol, we estimated that 2,000 children would enroll and complete follow-up with twice per week swabbing. Figure 1 provides the power (with two-sided alpha = 0.05) to reject the null hypothesis that VE=0 under various scenarios: VEs of 0.4, 0.6 and 0.8 and attack rates equal to or 0.5 to 2 times that observed in 2020. For example, if the attack is equal to 5.7 per 1,000 person-weeks with 6 weeks of follow-up, there is 80% power to detect a VE of 60%. If the attack rate is half that from 2020 (2.9 per 1,000 person-weeks) with 6 weeks of follow-up, then the study has >80% power to detect VE of 80%. These calculations assume all infections will be detected with twice per week swabbing.

[figure not shown]

Figure 1 Power to detect vaccine efficacy against infection with 2000 participants, assuming follow-up for 6, 12 or 20 weeks and incidence rate equal to 2.9 per 1,000 person-weeks (left panel), 4.8 per 1,000 person-weeks (center panel), and 5.7 per 1,000 person-weeks.

### 3. GENERAL DATA ANALYSIS CONSIDERATIONS

#### 3.1 Analysis Set(s)

For analysis purposes, the following populations are defined:

**Intention to Treat (ITT):** All enrolled participants who had at least one valid result in the lab results dataset

**Modified Intention to Treat (mITT):** All ITT participants who were not identified as having SARS-CoV-2 infection, either through RT-PCR or serological testing, prior to administration of the second dose of the first dosing series.

**Primary analysis set (PAS):** The intention of the SNIFF protocol was to enroll participants at their second dose of the first vaccination series and immediately start swabbing. This would allow exclusion of all participants who were previously infected. However, many participants enrolled after the second dose of the initial series, and it may be impossible to determine if they acquired infection in between that second dose and the first swab. We define this data set to account for this by limiting inclusion to mITT participants enrolled before 4 weeks post second dose of the initial series. Primary analyses will be conducted on this data set.

**Primary analyses set 2 (PAS2):** All mITT participants enrolled by July 12, 2021. Primary analyses will be conducted on this data set. This analysis set serves as a complement to PAS in case too many participants have enrolled after 4 weeks post second dose of the primary series. 82.4% were enrolled by this date.

**Post crossover analysis set (PCAS):** All mITT participants enrolled before 4 weeks post second dose of the crossover series without evidence of prior infection before or at the second dose of the crossover series.

**PCR-positive (PP-ITT):** All participants in the ITT population with SARS-CoV-2 RNA detected by RNA-RT-PCR as part of the SNIFF study (as determined by the lab).

**PCR-positive PAS (PP-PAS):** All participants in the PAS with SARS-CoV-2 RNA detected by RNA-RT-PCR as part of the SNIFF study (as determined by the lab).

**PCR-positive PAS (PP-PAS2):** All participants in the PAS2 with SARS-CoV-2 RNA detected by RNA-RT-PCR as part of the SNIFF study (as determined by the lab).

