#### 3.2 Statistical Analysis Issues

Key information such as product assignment (randomization), clinical symptomatology, adjudicated COVID-19 illness endpoints, RNA PCR results, demographics, risk factors, timing of vaccination, outside vaccination receipt date, and laboratory results (specifically seroconversion indicative of prior infection) are collected in the parent protocol. Those data will be sent to SCHARP after the study ends to merge with the SNIFF data for analyses.

This document was written without knowledge of the primary study database or access to any data summaries from the parent study, including enrollment characteristics of the population, and may need to be updated once this database is provided to the statistical team.

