## 9. PRIMARY EFFICACY/EFFECTIVENESS ANALYSES

### 9.1 Descriptive measures of SARS-CoV-2 acquisition:

*Table 1 Table for use when summarizing incident outcomes, including infection, overall and with and without COVID-defining symptoms.*

| Randomization arm  | Exposure                         | Number of participants | Number of incident endpoints | Person-years | Incidence rate (95% CI) |
|--------------------|----------------------------------|------------------------|------------------------------|--------------|-------------------------|
| Vaccine -> Placebo | Two doses of vaccine             |                        |                              | See note 2   |                         |
| Placebo -> Vaccine | Single dose of vaccine           |                        |                              | See note 1   |                         |
|                    | Two doses of vaccine             |                        |                              | See note 2   |                         |
|                    | Unvaccinated (two placebo doses) |                        |                              | See note 3   |                         |

Note 1: Total number of person-years post first dose and pre first of second dose in the crossover period, infection (maybe due to RT-PCR or antibody evidence of infection as per endpoints in analyses described below) or censoring.

Note 2: Total number of person-years post second dose and pre first of infection (maybe due to RT-PCR or antibody evidence of infection as per endpoints in analyses described below) or censoring.

Note 3: Total number of person-years post second dose of placebo and pre first of infection (maybe due to RT-PCR or antibody evidence of infection as per endpoints in analyses described below) or censoring.

The table above will be replicated by time periods, stratifying by calendar month as well as pre and post crossover. Results will be plotted over time. Additional calendar periods may be defined by predominant variant at the site with further stratification by the variant associated with the endpoint, recognizing that not all infections have enough virus present to be sequenced.

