### 9.2 Primary Objective: Prevention of Infection

#### Primary analysis

Endpoint: SARS-CoV-2 detected by RT-PCR on self-collected SNIFF-provided nasal swabs, right-censored at the last negative test at or before the earliest of the second dose of the crossover vaccination series (vaccine or placebo), 4 weeks post first crossover dose (applicable for cases where the second dose in the crossover period is missed or late), termination, or receipt of EUA vaccine.

Data sets: Primary analyses set; supported by analyses on the mITT set

Approach: Incidence of SARS-CoV-2 infection will be analyzed using a Cox Proportional Hazards model using follow-up time through 4 weeks post crossover. Calendar time will not be accounted for in the primary analysis since enrollment was completed in a short window of time. This analysis only counts infections until the second dose of the crossover series. Follow-up time may be right-censored earlier if a participant receives an EUA vaccine or otherwise is terminated early from the study. Randomization arm will be merged from the primary study database. Efficacy will be estimated as 1-HR (hazard ratio) from a Cox proportional hazards model. The primary analysis will not use any endpoint information collected in the parent study. This analysis will only include randomization as a covariate. The proportional hazards assumption will be assessed graphically.

#### Sensitivity analysis 1

The analysis will be repeated counting follow-up time up to 2 weeks post first dose of the crossover series.

Endpoint: SARS-CoV-2 detected by RT-PCR on self-collected SNIFF-provided nasal swabs, right-censored at the last negative test at or before the earliest of the second dose of the crossover series (vaccine or placebo), 2 weeks post first crossover dose (applicable for cases where the second dose is missed or late), termination, or receipt of EUA vaccine.

#### Supporting analysis 1

If any participants are identified as having infection in the parent study but not in the SNIFF study, the primary analysis will be repeated by revising the primary endpoint to include the first time to SARS-CoV-2 infection as defined in the parent study or SNIFF.

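### The prior-infection exclusion and the Table 1 person-time both start at dose 2, but swabbing can start weeks later; entry, exit and gap-infection rules need stating (small effect on VE)

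*Supplement*

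**What the plan says.** **Exclusion.** SAP v2.0 section 3.1 defines mITT by dropping participants identified as infected "either through RT-PCR or serological testing, prior to administration of the second dose of the first dosing series". PAS inherits this rule and adds a limit on enrolment delay by "limiting inclusion to mITT participants enrolled before 4 weeks post second dose of the initial series". mITT, the supporting set, has no such limit. The section admits that for late enrollees "it may be impossible to determine if they acquired infection in between that second dose and the first swab".

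**Data available.** Section 3.2 lists parent-study PCR results among the data to be merged, and states that "laboratory results (specifically seroconversion indicative of prior infection) are collected in the parent protocol".

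**Primary endpoint.** Section 9.2 defines it as "SARS-CoV-2 detected by RT-PCR on self-collected SNIFF-provided nasal swabs, right-censored at the last negative test at or before the earliest of" a list of events that includes crossover dose 2. It sets no condition on the first swab, and "The primary analysis will not use any endpoint information collected in the parent study". The origin of the Cox time scale is not stated there.

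**Descriptive rates.** In section 9.1, Table 1, Note 2 (two doses of vaccine) begins "Total number of person-years post second dose and pre first of infection". Note 3 (unvaccinated) begins "Total number of person-years post second dose of placebo and pre first of infection". Neither provides for later entry at enrolment or first swab. Note 1 (single dose) starts after the first dose and stops at the second crossover dose. Note 3 names only infection or censoring as its end.

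**Durability.** Section 10.2 puts the time origin at crossover dose 2, while section 3.1 lets the post-crossover set (PCAS) include participants enrolled up to 4 weeks after that dose.

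**The concern.** Three clocks are in use: dose 2 for the exclusion and for Table 1, enrolment for the section 9.1 plots, and the first swab for when an endpoint can first be observed. Where they differ, two things go wrong.

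First, a participant infected between dose 2 and the first swab is misclassified. If still shedding, the first swab is scored as an incident primary event. If recovered, the person contributes time at low risk. This happens even when the parent study has recorded the infection, because the exclusion stops at dose 2. Supporting analysis 1 adds parent-study infections but gives no lower time bound, so it does not settle how an infection before enrolment is handled.

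Second, person-time that starts at dose 2 contains a stretch in which no event can be recorded. Rates built that way are too low. Separately, the open end of Note 3 lets placebo-arm time after the first active crossover dose be counted in both the Unvaccinated and the Single dose of vaccine rows.

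At stake are the absolute incidence rates and, through misclassified events, the primary hazard ratio. PAS has only 13 and 21 events, so single reclassifications are visible.

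**Working it through.** **Inputs (Supplement Table S2; weeks per year 52.18)**

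| Set, censoring | Vaccine: N, events, PY | Placebo: N, events, PY |
|---|---|---|
| PAS, crossover dose 2 | 466, 13, 87.2 | 216, 21, 38.7 |
| PAS, crossover dose 1 | 464, 5, 62.6 | 216, 10, 28.4 |
| mITT, crossover dose 2 | 628, 16, 110.3 | 302, 28, 50.1 |
| mITT, crossover dose 1 | 620, 5, 76.3 | 301, 13, 35.3 |

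**1. Reproduce the reported rates.** Rate = events / PY × 100, with exact Poisson limits. PAS to crossover dose 2: 13/87.2 = 14.9 (7.9, 25.5) and 21/38.7 = 54.3 (33.6, 82.9). The table prints 14.9 and 54.2; the difference is rounding of PY. Crude VE = 1 − (13/87.2)/(21/38.7) = 72.5%, against the reported 73.5% (47.1, 86.7).

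**2. Which origin do the reported rates use?** Participants in mITT but not PAS enrolled at least 4 weeks after dose 2. By subtraction, their time to crossover dose 1 is:
- vaccine: 620 − 464 = 156 people, 76.3 − 62.6 = 13.7 PY, 4.6 weeks each
- placebo: 301 − 216 = 85 people, 35.3 − 28.4 = 6.9 PY, 4.2 weeks each

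Had time begun at dose 2, at least 4 of those weeks would precede swabbing. That leaves about 0.6 and 0.2 week of observation, in which 13 − 10 = 3 placebo events would have had to occur. This is implausible, so the reported rates appear to start at enrolment or first swab.

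**3. What Notes 2 and 3 would do if followed literally.** Mean PAS follow-up is (87.2 + 38.7) × 52.18 / 682 = 9.63 weeks. For a mean gap of g weeks (assumed; the documents give no distribution), the understatement is g/(9.63 + g), and each arm's rate is events / (PY + N × g/52.18).

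| g | Understatement | Vaccine rate | Placebo rate | Crude VE |
|---|---|---|---|---|
| 0 | 0% | 14.9 | 54.3 | 72.5% |
| 1 | 9.4% | 13.5 | 49.0 | 72.4% |
| 2 | 17.2% | 12.4 | 44.7 | 72.3% |
| 4 (PAS enrolment limit) | 29.3% | 10.6 | 38.0 | 72.2% |

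**4. Gap infections in PAS.** Using 2.9–5.7 per 1,000 person-weeks (SAP section 2.5) and a gap of 1–4 weeks:
- placebo: 216 × 1 × 0.0029 = 0.6, up to 216 × 4 × 0.0057 = 4.9
- vaccine, at VE 60%: 466 × 1 × 0.0029 × 0.4 = 0.5, up to 466 × 4 × 0.0057 × 0.4 = 4.3

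Only those still PCR-positive at the first swab would be scored as events. Removing events with PY held fixed gives these crude VEs:
- one per arm: 73.4%
- two per arm: 74.3%
- none vaccine, two placebo: 69.6%
- two vaccine, none placebo: 1 − (11/87.2)/(21/38.7) = 76.8%

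**5. The interval between crossover doses.** By subtraction:
- vaccine: 13 − 5 = 8 events in 87.2 − 62.6 = 24.6 PY, or 32.5 per 100 PY
- placebo: 21 − 10 = 11 events in 38.7 − 28.4 = 10.3 PY, or 107 per 100 PY

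Both arms rose sharply, about fourfold from 8.0 and threefold from 35.3.

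**6. How many PCAS participants could have pre-entry time?** SAP section 3.1 says 82.4% had enrolled by 12 July 2021 (denominator not stated). Protocol v4.0 section 2.1 dates the start of crossover at 10 August 2021, and the doses are 21 days apart. At most 17.6% could therefore have enrolled after crossover dose 2, and probably fewer.

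**The case against.** The SAP discloses the gap, and PAS was defined to shorten it; mITT is only supporting. The primary estimate is a Cox hazard ratio. Section 9.1 defines study time as time since enrolment for the plots, and section 12 treats study time as the default scale. Table 1 therefore does not feed the primary result. Its row labels also separate unvaccinated from single-dose time, so double counting requires reading Note 3 against its own row. PCAS already excludes evidence of infection up to crossover dose 2. All of this stands. It limits the size of the point but does not supply the missing entry, exit and first-swab rules.

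Four stronger readings are tempting and are not supported:

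- *That the published rates are diluted.* Step 2 indicates that they are not.
- *That the placebo change from 35.3 to 54.2 per 100 PY measures the Note 3 fault.* The vaccine arm, which received placebo at crossover, rose from 8.0 to 14.9 over the same windows. The change mostly reflects rising background incidence. Contamination by vaccinated time should in any case lower the rate.
- *That VE is materially biased by immune time.* With a 2-week gap at the pre-crossover rates, about 3.0 of 220 placebo (1.4%) and 1.4 of 471 vaccine participants (0.3%) would be infected before swabbing. If all were then immune, VE of 73.5% would move by about 0.3 points.
- *That first-swab positives must leave the primary analysis.* Section 2.2 counts infections on swabs from the day 21 visit or thereafter, so an infection acquired after dose 2 fits the endpoint as written. Excluding it is a post-randomisation exclusion on the outcome, and the choice is debatable.

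**Conclusion.** The point holds as a fault in the rules, not as a fault shown in the results. The exclusion stops at dose 2, no negative first swab is required, Table 1 Notes 2 and 3 admit time in which no endpoint can occur, Note 3 overlaps Note 1, and the durability origin can precede enrolment.

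Followed literally, Table 1 would understate absolute rates by about 9–17% for a mean gap of 1–2 weeks, while VE would move by about 0.2 points. Misclassified gap infections are the only route to the primary hazard ratio. Moving up to two events in either arm takes crude VE from 72.5% to between 69.6% and 76.8%, well inside the reported interval of 47.1–86.7%. The durability issue affects at most a minority of PCAS.

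These sizes rest on assumed gap lengths, on planning incidence applied to the gap, and on VE of 60% in the gap. The documents give neither the enrolment-delay distribution nor the number positive at the first swab.

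**What to change.** - In section 9.2, state the origin of the primary Cox time scale, and state that a participant enters the risk set at enrolment or at the first valid SNIFF swab.
- In sections 10.2 and 10.3, keep the crossover dose 2 origin but use delayed entry for anyone whose first swab comes later.
- In Table 1, start Notes 2 and 3 at the later of dose 2 and first swab, and end Note 3 at the first crossover dose.
- Add one sensitivity analysis of the primary endpoint that excludes participants with parent-study PCR or serological evidence of infection between dose 2 and first swab, and participants positive at the first swab. Report how many of each there are by arm. Leave the primary analysis as it is.
- In supporting analysis 1, say how a parent-study infection dated before SNIFF entry is handled.

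The cost is SAP wording and one extra analysis on data already being merged. The sensitivity analysis loses a few participants and events, and it can remove only gap infections that the parent study happened to detect or that the first swab shows.

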#### 3.2 Statistical Analysis Issues

Key information such as product assignment (randomization), clinical symptomatology, adjudicated COVID-19 illness endpoints, RNA PCR results, demographics, risk factors, timing of vaccination, outside vaccination receipt date, and laboratory results (specifically seroconversion indicative of prior infection) are collected in the parent protocol. Those data will be sent to SCHARP after the study ends to merge with the SNIFF data for analyses.

This document was written without knowledge of the primary study database or access to any data summaries from the parent study, including enrollment characteristics of the population, and may need to be updated once this database is provided to the statistical team.

### SARS-CoV-2 Viral Load

Viral load assessment will be conducted via digital PCR methods using N1 and N3 target sets and expressed in copies/swab on a per sample basis for all specimens with a “detected” interpretation.

### Change of predominant variant in the United States during follow-up time

From the first enrollment in this study to the end of follow-up, the predominant SARS-Cov-2 strain changed from alpha to delta (Figure 2). We will plan to repeat analyses in the subset of sites in states where delta was the most prevalent strain (>80%) at the start of enrollment (according to nextstrain.org).

### Durability analysis

This SAP reflects a version of the protocol in which durability was included as a secondary endpoint. Due to the changing prevalence of variants throughout the follow-up time and the expedited crossover timelines in the parent study, it will be challenging to estimate durability. First, the follow-up time for the group vaccinated early may be too short to expect a meaningful decline in efficacy. Second, durability estimates will be confounded by variant (see Figure 2).

[figure not shown]

Figure 2 Enrollment into SNIFF and prevalence of predominant variants in the United States over calendar time. Data on prevalence of variants is provided by nextstrain.org, accessed on 11/30/2021.

### 3.3 Incorrect/missing Swabbing Date

At times in the study, participants neglected to scan their swabs before returning them or scanned multiple swabs on the same date. Cases with evidence of an incident infection, either by receipt of a

swab with RNA detected by PCR, or evidence of infection from the parent study, will be reviewed by an adjudication committee to determine timing of infection.

#### **4. INTERIM ANALYSIS AND DATA MONITORING COMMITTEE**

No interim analyses were planned for this study nor was there a data monitoring committee.

#### **5. GENERAL ANALYSIS METHODS**

Descriptive statistics that will be used to summarize continuous variables are as follows: mean and standard deviation, median and interquartile range, quartiles, range, and number of missing data values. For categorical variables, descriptive statistics that will be used include the following: frequencies, relative frequencies, and the number of missing data values. Descriptive analyses summarizing baseline and follow-up data will be stratified by state. Line, scatter, and box plots will be used, as appropriate, for longitudinal data representations. Covariates from regression models will be assessed using Wald tests and corresponding 95% confidence intervals, unless otherwise specified. A two-sided alpha level of 0.05 will be used for all statistical tests, unless otherwise specified.

#### **6. TRIAL PARTICIPANT DISPOSITION**

##### **6.1 Disposition of Participant**

##### **6.1.1 Screening and Enrollment**

Dates of site activation, first enrollment, and last enrollment, as well as the number of participants screened, number and percentage of participants enrolled, and the screening-to-enrollment ratio will be displayed in a table overall and by site and randomization arm.

The number of participants included in each data set will be tabulated by site and randomization arm.

Reasons for participants who are not eligible for the study will be displayed in a listing.

##### **6.1.2 Compliance to Swabbing**

Participants are expected to swab on Mondays and Thursdays. Thus the weeks are separated into two collection windows – window 1 (Monday, Tuesday, Wednesday) and window 2 (Thursday, Friday, Saturday, Sunday). Alluvial plots will be used to capture completeness of swabbing. Categories: 0 windows, 1 window, or 2 windows per week, discontinued (exited study). These will be created to describe the population overall and by randomization arm.

The number of expected swabs versus resulted scanned swabs will be tabulated overall and by site and randomization arm.

